### Objectives and outcome variables

The trial main hypothesis is that the use of combination therapy with MTX and ADA will be more effective in inducing and maintaining ocular inflammatory inactivity than either drug given in monotherapy.

The *primary efficacy objective* is to establish which treatment strategy results in a higher proportion of subjects achieving a complete and maintained resolution of the ocular inflammation, on an intent to treat basis. The *primary efficacy outcome* will be the proportion of patients achieving a *Good Clinical Response* between the combination therapy arm and the single ISD arms. This outcome is defined as a complete resolution of the ocular inflammatory signs (including active chorioretinal lesions, active retinal vascular inflammation, uveitis macular oedema, presence of anterior chamber cells and presence of vitreous haze), achieved within the first 16 weeks of the study and maintained during follow-up until the end of the study (week 52); furthermore, there must not be a treatment failure due to safety or intolerability; the subject must adhere to the initial (up to week 16) oral GCs tapering protocol; all study visits from baseline to 16 weeks must be completed and at the final visit (week 52), the subject must be treated with up to 7.5 mg/day of oral prednisone (or equivalent) and up to two times a day of prednisolone acetate 1% (or equivalent). The *secondary efficacy objectives* and outcomes variables can be found at table 1.

**Table 1 T1:** Efficacy-related secondary objectives and outcome variables

Objective	Outcome variable
To compare the fraction of subjects who achieve a complete inflammatory ocular inactivity by week 16	Complete abrogation of the ocular inflammatory signs, which is achieved within the first 16 weeks of the study, no treatment failure due to safety or intolerability; compliance with the initial (up to week 16) oral GCs tapering protocol, and completion of all study visits from baseline to 16 weeks
To compare several Patient-Reported Outcomes Measures (health-related and vision-related quality of life, anxiety and depression) between treatment strategies	EuroQuol 5D-5L Visual Functioning Questionnaire-25 Hospital Anxiety and Depression Scale

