To compare the presence of the clinical components of the Good Clinical Response variable between treatment strategies during follow-up	Active chorioretinal lesions; active retinal vascular inflammation; macular oedema; ACC; vitreous haze and loss of CVA secondary to inflammation at baseline, week 16, week 52 and relapse visit
To compare the time to relapse after week 16 between treatment strategies	The time to inflammatory relapse between groups, defined as the time from visit 16 weeks until end of the study, loss of follow-up or appearance of at least one ocular inflammatory manifestation, in those individuals achieving a Good Clinical Response by visit 16 week
To compare the evolution of visual acuity during follow-up	Best-corrected visual acuity (BCVA) during follow-up
To compare the development of anti-adalimumab antibodies during the follow-up, between those subjects treated with monotherapy and combination therapy	Assessment of anti-ADA antibodies (AAA) at week 15, 27, 51 and relapse
To assess the cost-utility and cost-effectiveness from both a Health System and a Societal perspective of the combination therapy and the ADA monotherapy compared with MTX given alone	Direct and indirect cost, and incremental cost effectiveness ratios. Drug costs will be calculated individually for each patient taking as reference the price published in 2022 by the Health Ministry for the Spanish Health System. Outpatient and inpatient care, other medical cost, home care and productivity loss will be estimated based on the data from eSalud database^68^ and from the Minimum Basic Data Set of the Spanish Health Ministry.^69^

ADA, adalimumab; GC, glucocorticoid; MTX, methotrexate.

Security-related objective will establish which treatment strategy has better tolerability. Safety outcomes will be collected in the form of AEs, physical examination and laboratory tests throughout the treatment period and up to 70 days after the last dose in this study. Gender of the subjects will be taken into account.^53^

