### Authorised rescue medication

During whole study up to two inflammatory relapses (unilateral or bilateral) will be allowed, one during the first period (baseline–week 16: ACC relapse) and one during the second period (week 16–week 52: any location), before declaring the lack of response to the assigned medication. Based on the location and severity of the relapse, a protocolised rescue treatment with Topical AND/OR Local OR Oral GCs will be allowed. In case inflammation cannot be suppressed in 4 weeks, or a new relapse takes place after 4 weeks, it will be declared treatment failure and the subject will exit the study.

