### Study procedures

Study visits will be the baseline visit, visits at weeks 1, 4, and every 4 weeks thereafter until (a) the subject is determined as unable to achieve complete resolution of the ocular inflammatory process by week 16, OR; (b) the subject is determined as unable to maintain a complete resolution of the ocular inflammatory process, between weeks 16 and 52 OR; (c) the subject completes 52 weeks of this clinical trial, OR; (d) the study is stopped due to the findings of the Data Security Monitoring Board, OR and (e) the subject meets any of the study finalisation criteria.

Informed consent has to be acquired before carrying out any study procedure, including screening tests (online supplemental file 1 contains a sample informed consent). Before baseline (when the subject is randomised), several screening visits can take place up to 14 days before that visit, in order to obtain all the required complementary tests to assess eligibility. The visit window for all scheduled visits is ±3 days through week 4 and ±7 days for all visits following the week 4 study visit. Table 3 provides an overview of the study activities.

10.1136/bmjopen-2021-051378.supp1Supplementary data

**Table 3 T3:** Study activities

Activity	Screening	Baseline	w1	w4	w8	w12	w16	w20	w24	w28	w32	w36	w40	w44	w48	FET	Relapse	Unsch.	70-day follow-up
Informed consent	X																		
Inclusion/exclusion criteria	X	X																	
Medical/surgical history	X	X																	
History of tobacco and alcohol use	X	X																	
Uveitis history	X	X																	
Vital signs/weight/height	X	X														X	(X)		
Physical exam	X	X														X	(X)		
Symptom directed physical exam			X	X	X	X	X	X	X	X	X	X	X	X	X		X		
Chest X-ray	X															X*			
Cerebral MRI†	(X)																		
TB screening	X																		
Serum pregnancy test††	X	X	X	X	X	X	X	X	X	X	X	X	X	X	X	X			
Hepatitis B/C screening	X																		
Syphilis testing (FTA)	X																		
Randomisation		X																	
Best-corrected visual acuity testing	(X)‡	(X)‡		X	X	X	X	X	X	X	X	X	X	X	X	X	X		
Tonometry	(X)‡	(X)‡		X	X	X	X	X	X	X	X	X	X	X	X	X	X		
Slit lamp exam	(X)‡	(X)‡		X	X	X	X	X	X	X	X	X	X	X	X	X	X		
Dilated indirect ophthalmoscopy	(X)‡	(X)‡		X	X	X	X	X	X	X	X	X	X	X	X	X	X		
Fundus photography	(X)‡	(X)‡					X									X	X		
Optical coherence tomography	(X)‡	(X)‡		X	X	X	X	X	X	X	X	X	X	X	X	X	X		
EuroQol-5D	(X)‡	(X)‡		X	X	X	X	X	X	X	X	X	X	X	X	X	X		

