#### Planned methods of statistical analysis for efficacy-related objectives

The primary analysis will be a Mantel–Haenszel test (MHT), stratified by NIU location, comparing the combination therapy arm and the single ISDs arms (both arms combined), and performed in the ITT set. Achievement of the Good Clinical response will be considered the binary response variable: those subjects achieving a Good Clinical versus those not achieving the outcome (regardless the cause). The exposure variables will be the treatment arm: those subjects receiving combination therapy versus those receiving either monotherapy. Uveitis location will be the strata: intermediate uveitis versus posterior OR panuveitis. If the results of the primary analysis are significant, then pairwise comparisons using MHT stratified by NIU location will be carried out. P values of the pairwise comparisons will be adjusted using the Bonferroni method. No interim efficacy-related analysis will be carried out.

Secondary efficacy-related analyses are designed to test the hypothesis that treatment assignment affects a given outcome, after controlling for selected covariates. Details can be found at table 4.

**Table 4 T4:** Planned methods of statistical analysis for efficacy-related secondary outcomes

Outcome variable	Statistical analysis
Complete abrogation of the ocular inflammatory signs, which is achieved within the first 16 weeks of the study, no treatment failure due to safety or intolerability; compliance with the initial (up to week 16) oral GCs tapering protocol and completion of all study visits from baseline to 16 weeks	MHT, stratified by NIU location. If p-value<0.05, pairwise comparisons using MHT stratified by NIU location will be carried out with Bonferroni adjustment of the pairwise p-values
EQ5D	GEE models nested by patient^70 71^ and adjusted by study visit (continuous) and treatment arm (discrete) will be carried out, using a Gaussian family and Identity as link function. Different covariable structures will be tested (independent and exchangeable) and compared using the Bayesian Information Criteria. Time x study arm interactions will assess different effects of time in the evolution of the outcome by arm. P-value<0.05 will be considered as a significant interaction
Visual Functioning Questionnaire-25 Hospital Anxiety and Depression Scale	Changes between Baseline and w16, and the FET visit will be compared between treatment groups using ANOVA

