Active chorioretinal lesions; active retinal vascular lesions; macular oedema; ACC; vitreous haze and loss of CVA secondary to inflammation at baseline, week 16, week 52 and relapse visit	MHT, stratified by NIU location. If p-value<0.05, pairwise comparisons using MHT stratified by NIU location will be carried out with Bonferroni adjustment of the pairwise p-values
The time to inflammatory relapse between groups, defined as the time from visit 16 weeks until end of the study, loss of follow-up or appearance of at least one ocular inflammatory manifestation, in those individuals achieving a Good Clinical Response by visit 16 week	Time to relapse between arms will be analysed using log-rank test at a two-sided significance level of 5%. Dropouts due to reasons other than inability to maintain a Good Clinical Response will be considered as censored observations at the time of dropping out. Only subjects able to achieve a Good Clinical Response by visit week 16 will be analysed. We will consider both the time until the onset of the first inflammatory manifestation, each inflammatory manifestation, the first inflammatory manifestation that does not resolve in the following 4 weeks and each inflammatory manifestation that does not resolve in the following 4 weeks.
Best-corrected visual acuity during follow-up	GEE models
Assessment of anti-ADA antibodies (AAA) at weeks 15, 27, 51 and relapse	MHT, stratified by NIU location. If p-value<0.05, pairwise comparisons using MHT stratified by NIU location will be carried out with Bonferroni adjustment of the pairwise p-values
Direct and indirect cost, and incremental cost effectiveness ratios	Cost utility and cost-effectiveness analysis from the perspectives of the National Health System and the Society will be performed. EQ5D scores will derive utility values representing health related quality of life. QALYs will be calculated by the area under the curve assuming a linear evolution of EQ5D values between visits. The average number of QALYs per patient will be calculated for each study arms. Effectiveness will be defined using our primary efficacy outcome. An average cost per patient will be calculated for each study arm, including direct (drug cost, outpatient and inpatient care and other medical cost) and indirect cost (home care, productivity loss): Incremental cost-effectiveness ratios will be calculated, using the MTX monotherapy arm as comparison

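### Testing each inflammatory sign between arms at the relapse visit, read naturally, compares the mix of signs among relapsers and not the effect of treatment on each sign

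*Protocol article*

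**What the plan says.** Table 1 (Objectives and outcome variables) gives the objective as "To compare the presence of the clinical components of the Good Clinical Response variable between treatment strategies during follow-up". The signs are active chorioretinal lesions, active retinal vascular inflammation, macular oedema, anterior chamber cells, vitreous haze and inflammatory loss of acuity. Both Table 1 and Table 4 set four time points, ending "loss of CVA secondary to inflammation at baseline, week 16, week 52 and relapse visit".

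The method in Table 4 is "MHT, stratified by NIU location. If p-value<0.05, pairwise comparisons using MHT stratified by NIU location will be carried out with Bonferroni adjustment" for multiplicity. The text above Table 4 states the purpose: "Secondary efficacy-related analyses are designed to test the hypothesis that treatment assignment affects a given outcome", after controlling for selected covariates.

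The relapse visit is not a calendar visit. Study procedures says "Study visits will be the baseline visit, visits at weeks 1, 4, and every 4 weeks thereafter until" one of several end conditions is met, and Table 3 gives relapse its own column beside the scheduled weeks. Under Authorised rescue medication, "up to two inflammatory relapses (unilateral or bilateral) will be allowed" per subject, so a subject may have none, one or two. The main hypothesis is that the combination "will be more effective in inducing and maintaining ocular inflammatory inactivity than either drug given in monotherapy".

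**The concern.** Whether a subject has a relapse visit is itself an outcome, and the trial expects it to differ by arm. A between-arm test at that visit compares two groups selected after randomisation. Its null hypothesis is that, among relapsers, the share showing the sign is the same in each arm. The stated question is different: whether assignment changes how often subjects have the sign.

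The two can come apart in both directions. If the combination prevents all kinds of relapse equally, the shares among relapsers stay equal and the test sees nothing. If it prevents some kinds more than others, the relapses that remain are enriched for the other signs, and the combination looks worse on a sign it has not affected or has even reduced. A significant result would then lead on to pairwise tests and could be reported as harm on that sign.

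The pool of relapse visits is also uneven. The rescue section confines the allowed first-period relapse to anterior chamber cells and allows any location in the second period. The share of relapses with anterior chamber cells therefore depends partly on when they occur.

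**Working it through.** **Inputs from the protocol article.** The plan gives no figure for this comparison, so only the design size is taken from it. Sample size determination states 54 per arm, and 54 / 0.85 = 63.5, rounded up to 64. As a check, 66% against 43% with 1:2 allocation, two-sided 0.05 and 80% power needs 55 in the combination arm, close to the stated 54. As in the primary analysis, the combination (64) is set against both monotherapy arms pooled (128).

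**Assumptions.** The relapse rates are not in the documents. The strata are taken as 30% and 70% of subjects (19 v 38 and 45 v 90). Each subject has at most one relapse, with or without the sign.

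**Expected shares.** Let *a* be the proportion of randomised subjects with a relapse showing the sign, and *o* the proportion with a relapse not showing it. The relapser-only test compares *a* / (*a* + *o*) between arms. A test on all randomised subjects compares *a*.

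| Scenario | Combination *a*, *o* | Monotherapy *a*, *o* | Share among relapsers, combination v monotherapy |
|---|---|---|---|
| 1. All relapses halved, 40% to 20% | 10%, 10% | 20%, 20% | 10/20 = 50% v 20/40 = 50% |
| 2. All relapses 50% to 20% | 12%, 8% | 30%, 20% | 12/20 = 60% v 30/50 = 60% |
| 3. Sign equal, others 20% to 10% | 20%, 10% | 20%, 20% | 20/30 = 67% v 20/40 = 50% |
| 4. Sign equal, others 20% to 5% | 20%, 5% | 20%, 20% | 20/25 = 80% v 20/40 = 50% |
| 5. Sign equal, others 30% to 5% | 15%, 5% | 15%, 30% | 15/20 = 75% v 15/45 = 33% |
| 6. Sign 15% to 10%, others 30% to 5% | 10%, 5% | 15%, 30% | 10/15 = 67% v 15/45 = 33% |

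**Simulation.** 20,000 trials per scenario. In each stratum the Mantel-Haenszel statistic sums observed minus expected sign counts in the combination arm and divides by the square root of the summed hypergeometric variances. Rejection is at |z| > 1.96.

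| Scenario | Relapsers only | All randomised |
|---|---|---|
| 1 | rejects 5% | combination better 42% |
| 2 | rejects 5% | combination better 82% |
| 3 | combination worse 23% | rejects 5%, both directions |
| 4 | combination worse 57% | rejects 5%, both directions |
| 5 | combination worse 78% | rejects 5%, both directions |
| 6 | combination worse 50% | worse under 1%, better 15% |
| No effect | rejects 5% | rejects 5% |

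With no treatment effect the relapser-only test holds its level, so the distortion comes from selection on relapse and not from the test statistic. In scenarios 3 to 6 the mix among relapsers really does differ. The rejection is correct for the test's own null and misleading for the question the plan asks.

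**The case against.** **The denominator is inferred.** The row does not say that only relapsers are analysed, whereas the next row of Table 4 states its restriction to week-16 responders outright. If non-relapsers counted as sign-absent among all randomised, the selection described here would go. That stands as a caveat. But nothing in the article says so, and a value at a relapse visit most naturally belongs to someone who had one.

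**Relapse is analysed elsewhere.** A reader might infer that the trial cannot detect prevented relapses. The documents do not support that. Table 4 plans log-rank tests of time to relapse, including time to each manifestation, and the same row tests every sign at weeks 16 and 52. The log-rank analysis is limited to week-16 responders, so it does not replace a comparison of all randomised subjects, but the blindness belongs to this one time point.

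**Other tempting readings.** One could infer that the general multiple-imputation rule would fill in relapse visits that never took place. A visit that did not occur is not missing data, and the article does not say it would be imputed. One could also read these tests as showing which signs drive the primary result. The stated objective is only to compare the components.

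**The larger figures need strong assumptions.** The 57% and 78% require other relapses to fall by three quarters or more with no effect on the sign. That is fair; the moderate case gives 23%.

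**The obvious repair has its own flaw.** Study procedures ends visits for subjects who cannot reach resolution by week 16. Many of them may never have a relapse visit, and scoring them sign-free would favour the arm with more of them. Suppose 75% v 50% reach resolution, with the same 30% risk of a sign-bearing relapse afterwards. The proportions are then 0.75 × 0.30 = 22.5% v 0.50 × 0.30 = 15%, and the all-randomised test calls the combination worse in 25% of trials. This objection stands and shapes the fix.

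**Conclusion.** The point holds in a limited form. On its natural reading, the relapse-visit test conditions on an outcome of treatment and cannot say whether assignment affects a given sign. Under the assumed rates it has no more than its 5% level when all relapses are halved. It points against the combination in about 23% of trials in a moderate case and 57% in a stronger one, with the sign's incidence equal in both arms. These are illustrations: direction and size depend on relapse rates the documents do not give, on pooling the monotherapy arms and on the assumed strata.

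The reach is one time point of one secondary outcome. The sample size and primary analysis do not depend on it. Testing signs at baseline in the same row is a lesser weakness: randomisation makes that null true, so the test says nothing about treatment, though it harms no treatment inference.

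**What to change.** Drop the hypothesis tests at the relapse visit and tabulate the signs there descriptively by arm, with the number of relapsers as denominator. Tabulate the baseline signs without tests.

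If an inferential comparison of signs over follow-up is wanted, define it on all randomised subjects with the same strata: the proportion, or cumulative incidence, with each sign present at week 16 or at any later visit or relapse up to week 52. Subjects who stop because inflammation never resolved are counted by the signs present when they stop, not as sign-free. Subjects who leave for other reasons are treated as censored or as a competing event, with the choice stated in advance.

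The cost is a few lines of analysis-plan wording and a stated rule for early leavers. It uses data already collected under Table 3 and needs no added visit or procedure.

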#### Sample size determination

*ADA arm*: after 1 year (50 weeks) of treatment, 20.3% of NIU patients achieved an outcome similar to our *primary efficacy outcome*.^28^

*MTX arm*: after 6 months of treatment, 65% of NIU patients achieve also similar outcome;^64^ we estimate that of those patients, 18%^65^ and 16%^66^ will be unable to maintain our outcome due to AEs and inefficacy, respectively; therefore, at 1 year, 43% will achieve our *primary efficacy outcome*. This figure will be assumed as the percentage of subjects treated with monotherapy achieving the primary efficacy outcome.

*MTX+ADA arm*: we will assume that combination therapy will increase the percentage of subjects achieving our *primary efficacy outcome* by 23% compared with the monotherapy arms.

To detect statistically significant differences between groups with a power of 80% and a significance level of 0.05, it will be necessary to recruit 54 patients per study arm (162 in total). Since the follow-up period is 52 weeks, losses of 15% will be assumed, increasing the sample size to 64 patients per study arm (192 patients in total). In order to test the difference between the treatments, superiority or relevant clinical improvement has been considered from a delta of 5% of the effect.

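### Table 4 tests the six clinical signs at baseline as if they were treatment outcomes, and does not use the baseline sign in the week 16 and week 52 comparisons

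*Protocol article*

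**What the plan says.** Table 1 (Objectives and outcome variables) gives the aim of this analysis as "To compare the presence of the clinical components of the Good Clinical Response variable between treatment strategies during follow-up". Its outcome cell, and the matching cell in Table 4, list active chorioretinal lesions, retinal vascular inflammation, macular oedema, anterior chamber cells, vitreous haze and "loss of CVA secondary to inflammation at baseline, week 16, week 52 and relapse visit".

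Table 4 gives that row a single method: "MHT, stratified by NIU location. If p-value<0.05, pairwise comparisons using MHT stratified by NIU location will be carried out with Bonferroni adjustment". It makes no separate, descriptive provision for the baseline visit. The strata are defined in the text on the primary analysis: "Uveitis location will be the strata: intermediate uveitis versus posterior OR panuveitis".

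The sentence that introduces Table 4 reads: "Secondary efficacy-related analyses are designed to test the hypothesis that treatment assignment affects a given outcome, after controlling for selected covariates". It is followed by a pointer to Table 4 for the details. For this row Table 4 names no covariate other than location.

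**The concern.** There are two separate points.

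- **Baseline as a tested visit.** Subjects are randomised at the baseline visit, and baseline eye findings come from that visit or from screening up to 14 days before it (Table 3, footnote ‡). Assignment cannot affect them. Every baseline null hypothesis is true by design, so the test cannot address the stated purpose of the secondary analyses. Any small p-value is a false positive, and under the row's own rule it would set off pairwise tests.
- **Baseline sign unused afterwards.** Eligibility requires active disease within 180 days but no particular sign at baseline. Some subjects will therefore have macular oedema, for example, at entry and others will not. If that status predicts the sign at week 16 or week 52, a test stratified by location alone carries avoidable noise.

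At stake are stray baseline p-values in the report and some lost precision in a secondary analysis. The primary conclusion does not depend on either.

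**Working it through.** **1. The plan's own figures.** The only power statement is for the primary outcome, "with a power of 80% and a significance level of 0.05".
- Monotherapy rate: 0.65 × (1 − 0.18 − 0.16) = 0.429, the stated 43%. Combination: 43% + 23 points = 66%.
- Combination versus both monotherapy arms pooled (1:2), two-sided 0.05 and 80% power give 55 per arm against the stated 54. Power at 54 versus 108 is 79.7%.
- 54 / (1 − 0.15) = 63.5, so 64 per arm and 192 in total.

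The figures reproduce, and 64 versus 128 is the size used below. The article gives no power, sign prevalence or baseline-to-follow-up correlation for any component.

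**2. Baseline tests.** Six tests at 0.05 with all nulls true:
- expected false positives: 6 × 0.05 = 0.3
- chance of at least one, if independent: 1 − 0.95^6 = 0.265

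Positive correlation between signs would lower the second figure, so about 26% is an upper guide.

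**3. Power gain, by formula.** If ρ is the correlation between baseline and follow-up sign, then approximately

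power after adjustment = Φ[(z₀.₉₇₅ + z_power)/√(1 − ρ²) − z₀.₉₇₅].

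From an assumed 80% with ρ = 0.5: (1.960 + 0.842)/0.866 − 1.960 = 1.275, and Φ(1.275) = 0.899.

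| ρ | Power after adjustment | Gain (points) |
|---|---|---|
| 0.1 | 80.4% | 0.4 |
| 0.2 | 81.6% | 1.6 |
| 0.3 | 83.6% | 3.6 |
| 0.4 | 86.4% | 6.4 |
| 0.5 | 89.9% | 9.9 |

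**4. Power gain, by simulation.** Mantel-Haenszel tests, 20,000 trials per scenario, 64 versus 128, two-sided 0.05, two strata (location) against four (location × baseline sign). Assumptions: the overall test uses the same pooled contrast as the primary analysis, location splits 50/50, and no data are missing. All sign rates are assumed.

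With the sign seldom appearing in subjects who lacked it (3% monotherapy, 1.5% combination) and persistence of 50% versus 25%:

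| Baseline prevalence | Two strata | Four strata |
|---|---|---|
| 30% | 35–36% | 46% |
| 40% | 46% | 57% |
| 50% | 56% | 67% |

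With persistence of 60% versus 35%, the gains were about 13 to 15 points at 40% prevalence. In these scenarios the baseline-to-follow-up correlation is around 0.5 or somewhat higher, which agrees with step 3.

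The result depends on the appearance rate. Holding prevalence at 40% and persistence at 50% versus 25%, and halving appearance on combination:

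| Appearance on monotherapy | Gain (points) |
|---|---|
| 3% | 11 |
| 10% | 7 |
| 15% | 4 to 5 |
| 20% | 3 |
| 25% | 2 |
| 30% | 1 |

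A baseline odds ratio of 1 to 2 gives a gain of about 0 to 1 point.

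**5. Do four strata hold up?** With no treatment effect, the four-stratum test rejected in about 5% of trials (4.9% and 5.1% in two runs).

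**6. Chance imbalance.** At 40% prevalence the standard deviation of the baseline difference is √[0.24 × (1/64 + 1/128)] = 0.075. Multiplied by 0.50 − 0.03 = 0.47, this moves the week 16 difference by about 3.5 points. That movement is ordinary sampling error and is already in the variance of the location-stratified test.

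**The case against.** The strongest reply has four parts.

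- **The visit list may only say when signs are recorded.** Table 4 repeats the Table 1 cell, and the objective there is worded for follow-up. This is a plausible account of how baseline came to be listed. But Table 4 attaches a test to the whole cell, so the text as written tests baseline and needs correcting.
- **Covariates are promised.** The article says that secondary analyses control for selected covariates, and it refers elsewhere to a separate statistical analysis plan. This softens the second point but does not remove it, because the article refers to Table 4 for the details and that row names location alone.
- **The location-stratified test is sound.** It matches the randomisation stratum and the primary analysis, and it holds its error rate. This stands in full: adding the baseline sign improves a valid test.
- **The baseline sign may predict little.** Active disease is required only within 180 days before baseline, relapse at any location is foreseen between weeks 16 and 52, and 57% of monotherapy subjects (100 − 43) are expected to miss the primary outcome. New signs may therefore be common, and preventing them is itself a benefit. This also stands, and it is why the gain cannot be given as one figure.

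The 26% also rests on independence, which is doubtful for macular oedema and inflammatory loss of acuity.

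**Conclusion.** The point holds in a limited form. The baseline test has no inferential meaning and does not fit its own objective, whatever sign rates are assumed. The follow-up tests are valid but less precise than the collected data allow. The gain from using the baseline sign is roughly 1 to 14 points of power at 64 versus 128 under the assumed rates. It is about 10 only with a correlation near 0.5, that is, when the sign seldom appears in subjects without it at baseline, and near zero when the baseline sign is weakly prognostic.

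Two stronger readings are tempting and are not supported:

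- **That the plan loses about 10 points of power.** The documents give no sign rates, correlation or component power from which such a figure could follow.
- **That omitting the baseline sign biases the comparison, or that chance imbalance is a further harm.** Under randomisation neither is so. The 3.5-point shift is the same loss of precision seen from another side.

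These are secondary analyses, so the consequence is modest.

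**What to change.** In the Table 4 component row:

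- Remove baseline from the visits tested, and report the six signs at baseline by arm descriptively, without p-values.
- For week 16 and week 52, stratify the Mantel-Haenszel test by uveitis location and by presence of the same sign at baseline (yes/no). This gives four strata, in both the overall and the pairwise tests.
- Align the Table 1 outcome cell with its follow-up objective, for example by marking baseline as descriptive and as the stratification value.

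The cost is analysis wording only. The slit lamp, ophthalmoscopy, tomography, fundus photography and acuity data are already scheduled at screening or baseline in Table 3, so no visits, measurements or patients are added. With 192 subjects, four strata average 192 / 4 = 48 each, which the simulation shows to be workable under its assumptions.
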